### Outcome assessment

The trial will run for 18 months and outcome measurements will be assessed at baseline, and again at 6, 12 and 18 months by means of a clinical health check and a self-administered questionnaire. Anthropometric, and blood pressure measurements as well as fasting blood samples, will be taken by independent doctors and nurses from Peking University, who are blinded to group allocation. All participants will be instructed to fast overnight prior to each clinical health check for a minimum of eight hours. Blood samples will be analysed centrally at the CHC Laboratory blinded to group allocation.

#### Physical Examination

1. Anthropometric measurements: Weight will be measured by a beam balance scale and height by a stadiometer attached to a wall. BMI will be calculated as weight (kg) divided by height squared (m^2^) and waist circumference (cm) is measured at the level midway between the lowest rib margin and the iliac crest.

2. Blood pressure: Systolic and diastolic blood pressure will be measured in a sitting position using a mercury sphygmomanometer and measurements will be taken from the right arm. Subjects will be asked to rest for at least 5 minutes before measurements are taken. The first phase of Korotkoff sounds will be recorded as the systolic blood pressure, and the fifth phase as the diastolic blood pressure.

3. Fasting blood samples:

• A Hitachi 7060C Automatic Biochemistry Analysis System will be used to measure fasting plasma glucose, 2 hour postprandial glucose, homocysteine, total cholesterol, triglyceride, and high-density lipoprotein (HDL) cholesterol by standard enzymatic methods. A direct HDL cholesterol method will used.

• Low-density lipoprotein (LDL) will be calculated using the Friedewald formula [31]. LDL calculations will not performed if the triglyceride level is >4.5 mmol/L.

• HbA1c will be measured by a Bayer Healthcare DCA 2000+ analyser.

According to the Chinese Guidelines for Diabetes Prevention and Management [32], the cut-off points of 1.5 mmol/L, 4.5 mmol/L, 2.6 mmol/L, and 1.1 mmol/L will be used in reporting elevated triglycerides, and total, LDL, and HDL cholesterol values. Those having systolic blood pressure (SBP) higher than 130 mmHg and those having diastolic blood pressure (DBP) higher than 80 mmHg will be regarded as having elevated values [33]. Participants with BMI <24 kg/m^2 ^will be regarded as being of normal weight, ≥24 kg/m^2 ^but <28 kg/m^2 ^as overweight, and ≥28 kg/m^2 ^as obese [34,35]. Waist circumference beyond 85cm for men and beyond 80cm for women will be used as the cut-off points for central obesity [34,35].

#### Self Administered Questionnaire

The self administered questionnaire will be completed by participants at each clinical health check. The questionnaire covers the following areas: the participant's background information and socio-economic status, use of health services and health status [36], smoking status [37], alcohol intake [38], psychosocial distress [39,40], quality of life [41,42], diabetes self-care activities [43,44], diabetes management self efficacy [45,46], as well as self rated health which will be measured by SF-1, the first question of the SF-36 [47,48]. All measures used in the questionnaire have previously adapted to suit the Chinese context and have been validated in Chinese populations.

### Intervention

#### Control group

Participants in the control group will receive usual care from their CHC. This may include referral to diabetes specialists, traditional Chinese medicine physicians, and physiotherapists which form part of standard care as outlined in the Chinese Guideline for Diabetes Prevention and Management [32]. Participants in the control group will undergo assessment at baseline, and again at 6, 12 and 18 months. All control group participants will be informed of their results.

#### Intervention group

Participants who are assigned to the intervention group will receive a combination of telephone and face-to-face health coaching in addition to usual care from their CHC. The health coaching will be performed by experienced clinicians (community doctors and nurses). Prior to commencing work on the intervention phase, all health coaches will be required to complete a certified training program in coach assisted chronic disease management. The training program includes the study of key concepts in patient-centred communications, health psychology, epidemiology of key targeted illnesses and conditions, skills training in MI and behaviour change, program evaluation, clinical outcome measurement and the Happy Life Club™ intervention protocol.

The health coaches will aim to assist participants in achieving the treatment targets as outlined in the Chinese Guideline for Diabetes Prevention and Management [32], with the primary goal of treatment of HbA1c of less than 7%. An intervention manual will be used in the study to guide health coaches that utilises existing local guidelines and recommendations (e.g. Dietary Guidelines for Chinese Residents [49]). The initial step in each health coaching session will be to set the agenda for the session with the participant. This will be achieved by simply asking the participant "What would be helpful to talk about today?" Once the participant identifies a key issue for discussion, health coaches will utilise their skills in MI by assessing current behaviour in relation to the issue and exploring the motivation and commitment for change. If a participant displays a need and adequate commitment to change, the health coaches will work with the participant to establish a goal for behaviour change that outlines where, when and how the behaviour change will be performed.

In the first two months participants will receive two face-to-face and four telephone coaching sessions per month. The frequency of the sessions will decrease over the 18 month intervention period as shown in Figure 2 such that in the last six months of the intervention, participants will receive one face-to-face session per month and one telephone session per three months. This reflects the philosophy of the MI approach whereby over time coach input diminished as the participants gain confidence in self-management. While there is no preset time frame for each health coaching session, it is anticipated from the pilot study that the duration of each telephone session will be approximately 20 minutes, and the face-to-face session approximately 30 minutes. Coaches will record the length of each session.

**Figure 2 F2:**
[figure not shown]
**Frequency of health coaching**.

In addition to health coaching, participants in the intervention group will undergo assessment at baseline, and again at 6, 12 and 18 months. All intervention participants will be informed of their results.

### Statistical analysis

Descriptive statistics will be used to summarise characteristics of both CHCs and participants, with regards to baseline characteristics and patterns of mean change over time. Differences between the intervention and control conditions, on both primary and secondary outcomes, will then be evaluated using multilevel modelling analysis [50]. Multilevel modelling refers to a family of analytic techniques that are appropriate when data has a 'nested' structure, such as when individuals are nested within groups (e.g., patients in hospitals). Repeated measurements represent another type of hierarchical structure, whereby repeated measurements can be viewed as nested within participants. Multilevel modelling techniques, such as multilevel regression, have advantages over alternative methods traditionally used to analyse such repeated measures data (e.g., ANCOVA [51]). For example, multilevel analysis uses data from all available measurements to examine trajectories of change, rather than focussing on a single wave of data such as the final end-point measurement. Furthermore, multilevel analysis can tolerate an 'unbalanced' data-set, whereby participants can have varying numbers of measurements which are irregularly spaced [52]. As such, multilevel analysis does not exclude participants because of missing data or attrition from the study, and is thus consistent with 'intention to treat' principles. Finally, multilevel analysis can be adapted to incorporate more than one type of nesting, as in cluster-randomised trials, where: (1) repeated measurements are nested within participants; and (2) participants are nested within clusters (i.e., CHCs). Multilevel analysis explicitly models, and thus controls for variance at different levels of the hierarchical structure, and has thus been recommended for use with cluster-randomised trials [29].

Analyses will consider participant trajectories over time, and evaluate whether these differ according to levels of exposure to the intervention. Through multilevel analysis, variation in outcome scores will be partitioned across three levels, including: (1) variation in repeated measures within participants, modelled as a function of the initial level (intercept), linear trajectory, and Level-1 residual that may be autocorrelated and heteroscedastic (although different models of the Level-1 error covariance structure can be evaluated [53]); (2) inter-individual variation in the intercept and trajectory, specified as a function of the cluster mean and Level-2 residual assumed to be independently and normally distributed; and (3) variation in cluster means for both intercept and trajectory. The between-cluster variation in trajectory, specifically, is then modelled as a function of an intercept, Level-3 covariate (reflecting exposure to the intervention), and residual. The test statistic for the parameter reflecting experimental condition is used to test the null hypothesis of no treatment effect [54]. One-sided tests will be used in all instances, and a level of p < 0.05 will be used to evaluate statistical significance of the primary outcome. Secondary analysis will use the critical level of p < 0.001 to control Type I error probabilities due to testing across multiple outcomes.

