### Trial objective

To determine the effectiveness of the Happy Life Club™ intervention in improving the HbA1c level and metabolic, physiological and psychological profiles of participants at 6, 12 and 18 months compared with usual care.

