### Sample size

Based on conventional methods for estimating a sufficient sample size in a randomised trial with two conditions, and assuming that individuals are randomised to conditions, the number of participants needed is determined mainly by three parameters [27]. These parameters are: (1) the tolerable Type I error rate (assuming the null hypothesis); (2) the desired level of statistical power (assuming the alternative hypothesis); and (3) an anticipated effect size for a relevant test statistic (e.g., standardised mean difference). Consistent with general conventions, [27] the current study specified a 5% Type I error rate as tolerable and required 80% power. The primary outcome measure was glycosylated haemoglobin (HbA1c), measured on a continuous scale, and a recent meta-analysis evaluating psychological interventions to improve glycaemic control in patients with T2DM [21] indicates an expected standardised effect of 0.32 across studies. This was the anticipated effect size estimate specified in the current investigation. Based on these parameters, and using the G*Power 3.1 program [28] to conduct calculations, it was ascertained that a sample size of *n *= 306 (153 per group) would be sufficient to detect an effect size of 0.32 with 80% power, while maintaining 5% Type I error.

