## Discussion

This cluster RCT has been specifically tailored to the Chinese health care system and has the ability to make a large contribution to the evidence base for the management of patients with T2DM. It is hypothesised that the health coaching intervention delivered in this study will enhance the ability of patients to self-manage T2DM, leading to improved clinical and psychosocial outcomes, thus delaying diabetic complications. In addition, the components of metabolic syndrome and the risk factors for cardiovascular disease will be assessed.

To our knowledge, this is the first trial that combines both telephone and face-to-face health coaching in relation to T2DM management in China. Similar studies have been conducted in other countries, however these have primarily been telephone [57,58] or group based interventions [59,60]. Furthermore, this study will uniquely assess the benefits of intervention delivery for three time periods (6, 12 and 18 months), providing evidence for which is the optimal period of intervention.

This trial is being conducted in a real-world community health setting in China. By implementing the study in community health settings, this study empowers and builds capacity within the existing workforce. This approach embeds the study within community health settings, thereby increasing the generalisability of results [61].

The success of this study is reliant not only on the capacity of the participants to engage in behaviour change but also on the performance of individual health coaches. According to the spirit of MI, the therapeutic relationship is more like a partnership or companionship than expert/recipient roles [18]. It is therefore essential that health coaches are supported in their role. Several approaches have been incorporated into the intervention strategy to ensure coaches receive adequate support: following initial MI training, regular meetings will be scheduled with health coach coordinators; diaries will be kept by each health coach; and a peer support system will be implemented.

An additional challenge for this study will be to ensure that the back-translation of data collected remains an accurate representation of the original version. The use of two, independent, bilingual translators will increase the chances that the original meaning has been retained, will ensure literal accuracy and will help to detect mistakes [62].

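### The treatment test is a single difference in linear slope, so the model cannot estimate the separate 6-, 12- and 18-month effects named in the objective

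*Protocol article*

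**What the plan says.** The Trial objective asks for effects on HbA1c and on the metabolic, physiological and "psychological profiles of participants at 6, 12 and 18 months compared with usual care". The Discussion goes further and says that the trial will assess "three time periods (6, 12 and 18 months), providing evidence for which is the optimal period of intervention". Under Outcome assessment, "outcome measurements will be assessed at baseline, and again at 6, 12 and 18 months".

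The Statistical analysis section sets a three-level growth model. Within participants, the outcome is "modelled as a function of the initial level (intercept), linear trajectory, and Level-1 residual that may be autocorrelated and heteroscedastic". The intervention enters as a cluster-level covariate on the trajectory, and no arm term on the intercept is described. The parameter for experimental condition is the test of no treatment effect, one-sided at 0.05 for the primary outcome. The only flexibility offered is in the Level-1 error covariance, not in the shape of the mean over time. Apart from this model, the section promises only descriptive summaries of mean change.

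The sample size rests on a standardised mean difference: the cited meta-analysis "indicates an expected standardised effect of 0.32 across studies". Coaching tapers. "In the first two months participants will receive two face-to-face and four telephone coaching sessions per month", and in the last six months "participants will receive one face-to-face session per month and one telephone session per three months".

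**The concern.** The objective asks for three differences and the model has one treatment parameter. The numbers it would give at 6, 12 and 18 months are multiples of one slope, not separate estimates. The claim about the optimal period is then settled by the form of the model: a beneficial slope makes the last visit best by construction.

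Linearity is also open to doubt in this trial. Planned contacts fall from 2 + 4 = 6 per month to 1 + 1/3 = 1.33 per month. An early drop in HbA1c followed by a plateau or some loss is therefore possible. In that case the reported 6-month effect would be far too small, and a benefit that faded could be missed by the primary test.

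**Working it through.** **The plan's own sample size.** For a difference of 0.32 SD, two-sided 5% and 80% power: 2 × ((1.96 + 0.84)/0.32)² = 153.3 per group, which matches the stated 153 per group (306). With 60 × 0.8 = 48 analysed per CHC and ICC 0.05, the design effect is 1 + 47 × 0.05 = 3.35. The effective sample is 22 × 48/3.35 = 315, with power 81%. The sizing reproduces, but for a difference in means and not for a slope.

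**What the slope forces (no assumption needed).** If the arm effect acts only on a linear trajectory, the differences are 6b, 12b and 18b. The 6-month figure is always one third of the 18-month figure.

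**What the slope estimates when the truth is not linear.** Inputs from the protocol: visits at 0, 6, 12 and 18 months, 11 CHCs per arm, 48 analysed per CHC, ICC 0.05. Assumptions: exchangeable correlation 0.5 between visits, applied to the arm differences; unit SD; 20 degrees of freedom; and a common baseline mean, because the text puts no arm term on the intercept. Benefit is counted as positive.

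- Variance of an arm difference at one visit: c = 2 × 3.35/(48 × 11) = 0.01269.
- Generalised least squares with a common baseline weights visit t by t − 0.2 × 36 = t − 7.2. The divisor is 504 − 0.2 × 36² = 244.8. Here 504 = Σt², 36 = Σt and 0.2 = 0.5/(1 + 3 × 0.5).
- Slope-implied 18-month effect: 18 × (−1.2·d6 + 4.8·d12 + 10.8·d18)/244.8.
- Its standard error: 18 × √(0.01269 × 0.5/244.8) = 0.092.
- 18-month contrast, standard error: √(0.01269 × (1 − 0.25)) = 0.098.
- Average over the three visits, standard error: √(0.01269 × (2/3 − 0.25)) = 0.073.

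Slope-implied 18-month effects:

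- Plateau 0.32/0.32/0.32: 18 × 4.608/244.8 = 0.339, hence 0.339/3 = 0.113 at 6 months.
- Fade to half, 0.32/0.24/0.16: 18 × 2.496/244.8 = 0.184.
- Fade to zero, 0.32/0.16/0: 18 × 0.384/244.8 = +0.028.

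Power from the noncentral t distribution:

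| True effect at 6/12/18 months (SD) | Slope, two-sided 5% | Slope, one-sided 5% | 18-month contrast, two-sided | Average over visits, two-sided |
|---|---|---|---|---|
| Ramp 0.11/0.21/0.32 | 91% | 96% | 88% | 80% |
| Plateau 0.32/0.32/0.32 | 94% | 97% | 88% | 99% |
| Fade to half 0.32/0.24/0.16 | 48% | 61% | 34% | 88% |

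For the fade to zero, the slope has about 9% power one-sided.

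**Sensitivity.** With a common baseline, within-person correlation about 0.6, cluster slope variance of 0 to 0.05 SD² and participant slope variance of 0 to 0.2 SD² over 18 months, the one-sided slope test has these powers:

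- ramp: 87% to over 99%;
- plateau: 82% to over 99%;
- fade to half: 30% to 81%.

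In the fade to zero, the implied 18-month effect is +0.028 at correlation 0.5. It is about −0.005 to −0.03 at correlations of 0.7 to 0.9.

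**The case against.** A test of arm by linear time in a three-level model is valid and recognised, and its Type I error is unaffected. A reader might infer that a front-loaded intervention would be missed, or its benefit reversed in sign. The document does not support that reading, for three reasons.

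- **A held benefit is not missed.** Under the model as described, a plateau has 94% power against 91% for a true ramp at correlation 0.5. With slope variance added it is at most about 4 points lower (82.5% against 86.7%).
- **Sign reversal is a corner case.** With a common baseline and correlation 0.5 it needs d6 > 4·d12 + 9·d18, which is almost complete loss by month 18. Separate arm intercepts would give worse figures: 19% two-sided for the fade to half, and −0.048 for the fade to zero. The text describes no arm term on the intercept.
- **The time course is not documented.** Nothing in the protocol gives HbA1c over time. Coaching tapers because participants are expected to gain confidence, and monthly face-to-face contact continues to the end. That fits a sustained benefit as well as a fading one.

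It is also fair to say that an 18-month primary contrast would not rescue a faded benefit, since it has 34% power where the slope has 48%.

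All of this stands, and it limits the power argument. It does not touch the mismatch with the objective. Descriptive means over time are not estimated treatment effects. Nor is this a detail left to an analysis plan, because the linear form and the single test are stated outright.

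**Conclusion.** The point holds as a mismatch between objective and model. The 1:2:3 constraint follows from the stated model alone: it cannot give separate effects at 6, 12 and 18 months, and it cannot show which period is optimal. A benefit constant from month 6 would be understated at that visit by about two thirds (0.11 against 0.32), with no loss of power at correlation 0.5.

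Material power loss is conditional on the benefit fading: 48% two-sided or 61% one-sided for a fade to half. An estimate near zero or slightly negative arises only when the benefit is almost wholly lost by month 18. These figures rest on the assumed within-person correlation and variance components, and an early drop is only a possibility suggested by the taper. I rate this as should-fix: the test is valid, but it does not answer the question that the protocol sets.

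**What to change.** Keep the three-level structure. Enter time as a categorical factor (baseline, 6, 12 and 18 months) with arm-by-visit terms, and use a common baseline mean or baseline HbA1c as a covariate. Report the arm differences at 6, 12 and 18 months with confidence intervals. Name one primary contrast in advance, either the 18-month difference or the average over visits. The linear slope may stay as a supportive analysis.

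The change is to wording only and needs no new data. The cost is some power, depending on the contrast (two-sided, correlation 0.5):

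- **18-month difference:** less than the slope under a ramp (88% against 91%), a plateau (88% against 94%) and a fade to half (34% against 48%).
- **Average over visits:** less under a ramp (80% against 91%), more under a plateau (99% against 94%) and a fade to half (88% against 48%).

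The choice should follow from which effect the trial most wants to claim, and be fixed before outcome data are seen.

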### Study population & setting

The study will be implemented at CHCs in the Fengtai District of Beijing, China. This district is a large residential community in southwest Beijing with a population of 1.823 million residents and an average life expectancy of 78.7 years [26]. Conveniently located within communities, CHCs deliver primary health care and basic health care to Fengtai residents. The socio-demographic profile of residents in Fengtai varies according to geographic location. West Fengtai is predominantly a regional/rural area; Central Fengtai is a residential suburban area; and East Fengtai is an urban area located near downtown Beijing.

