### Randomisation

Randomisation will be performed prior to baseline assessment of participants and CHCs will be the unit of randomisation. A member of the research team, blinded to CHC identity, will be responsible for central randomisation. Firstly, CHCs will be stratified by geographical location (east, central, and west) in order to achieve balanced groups according to socioeconomic status. Following stratification, CHCs will be randomly allocated into the control or intervention groups using block randomisation by computerised random allocation software.

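### Randomisation is stratified by region, but the stated trajectory model has no region term, so precision is forgone to the extent that region predicts the HbA1c trajectory

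*Protocol article*

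**What the plan says.** The Randomisation section states that "CHCs will be the unit of randomisation" and that "CHCs will be stratified by geographical location (east, central, and west) in order to achieve balanced groups according to socioeconomic status". Within strata, CHCs are "randomly allocated into the control or intervention groups using block randomisation by computerised random allocation software". Neither the block size nor the number of CHCs per stratum is given. The Study population & setting section supplies the background: "The socio-demographic profile of residents in Fengtai varies according to geographic location".

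The Statistical analysis section describes a three-level growth model. Level 3 covers "variation in cluster means for both intercept and trajectory". Between-cluster variation in trajectory "is then modelled as a function of an intercept, Level-3 covariate (reflecting exposure to the intervention), and residual". The decision rule follows: "The test statistic for the parameter reflecting experimental condition is used to test the null hypothesis of no treatment effect", and "One-sided tests will be used in all instances, and a level of p < 0.05 will be used" for the primary outcome. Region appears nowhere in that section.

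**The concern.** Stratifying by region removes between-region variation from the comparison of arms. If the model then omits region, that variation stays in the cluster-level residual, and the reported standard error describes a less precise design than the one actually run. Intervals become too wide and the test too conservative. With the number of clusters fixed at 22, precision lost this way cannot be bought back by adding CHCs.

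A smaller point concerns the covariate, which is described in terms of exposure to the intervention. It would be clearer as the arm to which the CHC was allocated.

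**Working it through.** **Inputs from the article (Sample size, Statistical analysis):** 22 CHCs; 60 participants per CHC; 20% attrition, so 60 × 0.8 = 48 analysed; ICC 0.05; standardised effect 0.32; 5% type I error and 80% power; one-sided tests in the analysis.

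**Assumptions (not in the article):** region explains a share q of the between-CHC variance; strata of 8/8/6 CHCs (7/7/8 as a check), closely balanced within strata; the outcome ICC of 0.05 is applied to the trajectory contrast.

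**Step 1: the plan's own figure.** The normal formula gives 2 × (1.960 + 0.842)² / 0.32² = 153.3, so 154 per group (308 in total). The t-test gives 310. The article has 306, which agrees for a two-sided test only; one-sided gives 242 to 244. The design effect is 1 + (48 − 1) × 0.05 = 3.35. Then 306 × 3.35 = 1025 analysed, and 1025 / 0.8 = 1281 recruited. The planned 1320 covers this, with two-sided normal-theory power of 0.811. The sample size is reproduced, and it takes no credit for stratification.

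**Step 2: standard error with and without region.** The variance of a CHC mean is 0.05 + 0.95/48 = 0.0698. With 11 CHCs per arm, SE = √(4 × 0.0698 / 22) = 0.1126 without region. With region in the model, 0.05 is replaced by 0.05(1 − q). The ratio of the two SEs is √[0.0698 / (0.0698 − 0.05q)].

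Type I error and power below come from simulation (8,000 runs per setting, strata 8/8/6, one-sided 5%, t tests on 20 degrees of freedom without region and 18 with).

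| q (assumed) | SE with region | SE ratio, without/with | Type I error, without region | Power, without vs with |
|---|---|---|---|---|
| 0 | 0.1126 | 1.00 | 0.052 | 0.864 vs 0.863 |
| 0.10 | 0.1085 | 1.04 | 0.048 | 0.869 vs 0.880 |
| 0.25 | 0.1021 | 1.10 | 0.036 | 0.887 vs 0.916 |
| 0.50 | 0.0902 | 1.25 | 0.019 | 0.909 vs 0.964 |

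With region in the model, type I error stays between 0.050 and 0.052. The Monte Carlo error near 5% is √(0.05 × 0.95 / 8000) = 0.0024, so 0.052 is not inflation. Strata of 7/7/8 give the same pattern: at q = 0.50, type I error without region is 0.022 and power is 0.895 vs 0.955.

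**Step 3: what omission does to the estimate.** In the null runs (8/8/6), the model SE without region against the true sampling SD was 0.1125 vs 0.1120 at q = 0, 0.1137 vs 0.1025 at q = 0.25, and 0.1151 vs 0.0909 at q = 0.50. The true SD was the same with and without region in the model. The estimate already benefits from the stratification; only its reported SE does not.

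**Step 4: level or slope.** Steps 2 and 3 treat the contrast as a cluster mean, whereas the tested parameter is a slope. A separate simulation of slopes used four visits, 48 complete participants per CHC, strata 8/8/6, an assumed between-CHC slope variance of 0.05, and one-sided 5% tests:
- Region explaining 50% of between-CHC variance in HbA1c *level*: type I error 0.050 without region and 0.051 with; power 0.892 vs 0.887. Omission costs nothing.
- Region explaining 30% of between-CHC variance in *slope*: type I error 0.030 vs 0.050; power 0.919 vs 0.952.

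What matters is therefore whether region predicts change in HbA1c, not whether it predicts level.

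**The case against.** The best counter-argument is that the harm is conditional. The article links region to socio-demographic profile and socioeconomic status, and never to change in HbA1c. A regional difference in level goes largely into the CHC intercept, which the model lets vary. A reader might infer that the standard errors are bound to be too large; the documents do not support that, and step 4 shows a case with no overstatement. This part of the objection stands.

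It also stands that the trial does not fall short of its planned power on this account. Without region, one-sided power is 0.864 to 0.909 across the assumed shares, above the 80% planned. The loss is a gain not taken. Nor is validity at risk, because type I error is at or below nominal.

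A reader might take the exposure wording to mean an as-treated or coaching-dose analysis. The text does not bear that out: the same section refers to experimental condition when it describes the test, and it invokes intention-to-treat principles. The wording is loose, no more.

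Lastly, a condensed article may leave adjustment covariates to an analysis plan. That would excuse silence. Here the article lists the terms of the tested equation, and the stratification factor is not among them. This part of the objection does not remove the mismatch.

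**Conclusion.** The point holds in conditional form. The Level-3 trajectory equation as stated omits the factor by which the CHCs are stratified. If region explains 10% to 50% of the between-CHC variance in trajectory, the standard error is about 4% to 25% too large, and one-sided power of about 0.88 to 0.96 becomes about 0.87 to 0.91. If region explains none of it, nothing is overstated. There is no bias and no excess of false positives.

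These sizes rest on the assumed shares, the assumed stratum sizes, near balance within strata, and the use of the outcome ICC for the trajectory contrast. The article gives no figure for any of the four. If the blocks left the arms less balanced within regions, the overstatement would be smaller, and adjustment would instead correct the chance imbalance.

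**What to change.** Add two region indicators (central and west, with east as reference) to the Level-3 equations for both the intercept and the trajectory, that is, region and region-by-time terms. A region main effect alone would not reach the tested slope. Use small-sample degrees of freedom at cluster level, and apply the same model to the primary and all secondary outcomes. Define the intervention covariate as the CHC's arm as randomised.

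Region is known for every CHC before randomisation, so no data collection is needed. The cost is two of about 20 cluster-level degrees of freedom (20 to 18). If region is irrelevant, that is at most about one point of power: one-sided 0.864 to 0.863 with strata of 8/8/6, and 0.864 to 0.857 with 7/7/8. Fixing the model before outcome data are seen also rules out a later choice between adjusted and unadjusted results.
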